### f) Analysis

The primary statistical analysis aims to measure effectiveness in a pragmatic real life context; this will be an analysis by allocated treatment (based on all families allocated to the intervention group regardless of whether they attended the programme), using mixed univariate and multivariate analysis of variance, taking into account level of attendance, programme fidelity and differences in the characteristics of the two groups as measured by collection of data from parents at baseline: parental age, marital status, housing tenure, income, ethnicity, parental health (including mental health) and recent stressful life events. As a supplementary analysis the potential of the programme to enable parents to change will be assessed in a regression analysis based on numbers of sessions attended (efficacy analysis).

Secondary analyses will be undertaken of all other outcome measures adopting first an allocated treatment approach using mixed univariate and multivariate methods as above followed by an efficacy analysis.

Intra class correlations will be assessed for all the main outcome measures and multilevel modelling used to take into account any design effects as well as the non independence of data from multiple children in one family.

A cost consequences analysis, which allows an array of outcome measures to be considered alongside the cost of the programme will be undertaken to compare FLNP with no intervention in parents and children from public purse, societal and parents' perspectives. Modelling will examine the sensitivity of the results to a range of assumptions.

Video recordings of sessions will be analysed using an agreed structured coding framework to assess the extent to which facilitators achieved programme fidelity and the skills of the facilitator, with a simple 1-5 fidelity rating applied to each programme.

For the qualitative interviews an iterative thematic analysis will be undertaken using data from all sources independently and results 'triangulated' across these to identify areas of commonality and difference.

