### b) Sample size calculation

We aimed to recruit 144 families into each of the control and intervention groups (288 in total) This sample size will be sufficient to detect an effect size of 0.4 at 85% power and alpha of 0.05 in the primary outcome measure. An effect size of 0.4 is the level of difference which could be expected on the basis of changes observed on objective measures of parenting in recent UK trials of the IYs programme [25,41], in the majority of trials included in systematic reviews [21,22] and in a before and after study of FLNP [40] using self report measures. The control families are offered FLNP after data collection at six months 'post intervention' is complete.

Since the intervention is offered to groups a cluster design effect is included in the analysis. Such design effects are typically small in parenting programme trials. One recent study of the IYs programme in which both randomisation and intervention were subject to design effects identified intra-class correlations attributable to 'group' effects ranging from 0 to 0.16 [25]. In our study, potential design effects would be attributable to the group-based nature of the intervention only, as randomisation is being undertaken at the level of individual families. If the intra-class correlation in our trial is as high as 0.178, a sample of 288 will be sufficient to detect an effect size of 0.6.

Families who do not attend or dropout will be followed up alongside other families. We anticipate a 20% loss to follow-up at 6 months post-intervention based on the results of other trials [42].

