The objective measures of parenting (the video and speech sample) are collected during a home visit to the families in the two months before the programme starts and again six months post programme. Self-completion questionnaires are collected pre intervention, immediately post intervention, and six months post programme. Videos of parenting and five minute speech samples are coded up by researchers who do not know the families and all data analyses will be carried out blind to group allocation.

Cost consequences are being established using health, social service, educational psychology or criminal justice service contacts for children and parents, and use of voluntary sector services; parental expenditure and time away from work attributable to these events or to involvement in the FLNP. Unit costs will be attached using routine data sources [52]. The cost consequences analysis will provide a clear descriptive summary of the results for each of the outcome measures set against the cost of FLNP.

The views and perceptions of families receiving the programme are being assessed by interviews with 12 parents who decline to take part in the research study to determine possible ways of improving recruitment and 12 intervention group parents representing different cultural and social backgrounds and different experiences (positive and negative) within the group, to gather information on the most and least valued aspects of programme, rating of the facilitators, and ways of improving the programme.

Programme fidelity is being assessed using video recordings of three random sessions in each programme (with parental consent) coded by Family Links staff. In addition both the parent and facilitator evaluation forms for the recorded sessions will be reviewed by Family Links. Uptake rates; attendance rates (number of sessions attended); dropout rates; mother/father ratio of attendees and attendance and dropout by day and time of group are also being measured.

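### The primary analysis is defined by allocation regardless of attendance, yet the same sentence adjusts it for attendance and programme fidelity, which arise after randomisation and have no meaningful value in control families

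*Protocol article*

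**What the plan says.** All of the analysis wording is in section f) Analysis of the protocol article.

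- Purpose: "The primary statistical analysis aims to measure effectiveness in a pragmatic real life context".
- Population: by allocation, "based on all families allocated to the intervention group regardless of whether they attended the programme".
- Adjustment, in the same sentence: "taking into account level of attendance, programme fidelity and differences in the characteristics of the two groups". The phrase that follows, "as measured by collection of data from parents at baseline: parental age, marital status, housing tenure, income, ethnicity, parental health" (the list ends with recent stressful life events), places the group characteristics at baseline. It does not cover attendance or fidelity, which are not on that list.
- The next sentence gives sessions attended a separate supplementary regression, called the efficacy analysis.
- The secondary outcomes are to be analysed by allocation with the same kind of methods.

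Section e) Outcome measures describes the two variables: "attendance rates (number of sessions attended") and "Programme fidelity is being assessed using video recordings of three random sessions in each programme". Section f) adds that fidelity is scored "with a simple 1-5 fidelity rating applied to each programme". Section c) Recruitment places randomisation at the consent and baseline visit. Section b) Sample size calculation says: "The control families are offered FLNP after data collection at six months 'post intervention' is complete".

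**The concern.** An analysis by allocation protects the comparison because allocation is random and the covariates are fixed before it. Attendance and fidelity are produced by allocation. Control families have, by design, no sessions before the six-month endpoint and no delivered programme to rate.

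This is the main test of Aim 1, effectiveness. If benefit comes through sessions, adjusting for sessions takes that benefit out of the arm term. If families who attend differ in prognosis from those who do not, the adjustment brings that difference into a comparison that randomisation had balanced. If neither holds, it still costs precision.

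**Working it through.** **1. The plan's own figure.** Inputs from section b): effect size 0.4, 85% power, alpha 0.05 (sidedness is not stated; two-sided assumed), 20% loss.

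- n per arm = 2(1.960 + 1.036)² / 0.4² = 112.2, so 113.
- Allowing for loss: 113 / 0.8 = 141.25, so 142 per arm and 284 in total, against the planned 288. The figure reproduces closely.
- Expected analysed families: 144 × 0.8 = 115 per arm, with 85.8% power before any clustering.

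**2. What the arm coefficient becomes.** Take a linear model with arm and sessions attended, controls coded 0. The slope on sessions, β, is then estimated from the intervention arm alone, and

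adjusted arm coefficient = (mean intervention − mean control) − β × (mean sessions in the intervention arm).

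This is the contrast between controls and an intervention family with no sessions. Adding fidelity coded 0 in controls moves the contrast to zero sessions and zero fidelity, a value outside the 1-5 scale.

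**3. What this gives.** The article reports no attendance or fidelity distribution and no relation of attendance to prognosis. The assumed inputs are: 20% never attend, mean 5.35 of 10 sessions, outcome SD 1.

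- Allocation effect 0.40, fully proportional to sessions: β = 0.40 / 5.35 = 0.075 per session, and 0.40 − 0.075 × 5.35 = 0.00.
- Constant effect 0.40, attendance unrelated to prognosis: β = 0, so the coefficient stays at 0.40.
- No effect, better-prognosis families attend more: a slope of 0.19 / 5.35 = 0.036 per session gives 0 − 0.19 = −0.19. If they attend less, the sign reverses to +0.19.

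**4. Simulation.** Ordinary least squares, 115 per arm, 3000 replicates, fidelity drawn evenly from 1-5 in groups of 8. The prognosis link is a family trait that drives attendance and has a loading of 0.3 on the outcome. Clustering of outcomes is ignored. Cells show mean arm coefficient; mean standard error; share of trials with p < 0.05.

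| Assumed truth | Arm only | Arm + attendance | Arm + attendance + fidelity |
|---|---|---|---|
| 0.40, proportional to sessions, no link | 0.40; 0.13; 86% | 0.00; 0.20; 5% | 0.00; 0.29; 5% |
| 0.40, proportional to sessions, link | 0.40; 0.14; 84% | −0.19; 0.20; 15% | −0.19; 0.29; 10% |
| 0.40, constant, no link | 0.40; 0.13; 86% | 0.40; 0.20; 51% | 0.40; 0.29; 28% |
| 0.40, constant, link | 0.40; 0.13; 87% | 0.21; 0.20; 19% | 0.22; 0.29; 12% |
| No effect, link | 0.00; 0.13; 5% | −0.19; 0.20; 16% | −0.19; 0.29; 10% |

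Reversing the link gives +0.19 under no effect and about 0.60 under a constant effect of 0.40. A second set of assumptions (25% never attending, a different link) with attendance alone gave −0.21 and 23% rejection under no effect, and +0.20 and 22% with the link reversed. With a constant effect and no link, its standard error rose from 0.13 to 0.17 and power fell from 86% to 65%.

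**5. Another coding.** If attendance is entered only within the intervention arm and centred on that arm's mean, the subtracted term in step 2 is zero and the arm coefficient equals the unadjusted one. A simulation of this coding gave 0.399 with 85% power for the proportional effect (84% unadjusted), and 0.002 with 4.6% rejection under no effect.

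**The case against.** The strongest reply is that the article fixes no model. Taking something into account is loose wording and may have been meant for exploratory or within-arm work. The intent, all allocated families whether or not they attended, is clear, and a full analysis plan may specify the model properly. It is true that coding is not stated, and step 5 shows that one coding leaves the allocation effect intact. But this is not detail left out. The two terms are named in the primary-analysis sentence, while attendance has its own supplementary analysis in the next. Covariate adjustment is the ordinary way to follow that sentence, and it contradicts the definition by allocation.

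Three stronger readings are tempting, and the documents do not support them.

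- A reader might infer that the bias has a known direction. It does not: the sign depends on who attends, and with a constant effect and no link there is no bias.
- A reader might infer that the primary test will have about 5% power. That figure holds by construction, because the scenario makes the whole effect proportional to sessions and then conditions on sessions. Nothing in the article says the effect works that way.
- A reader might infer that controls must either drop out of the model or be given an invented fidelity value. A centred term nested in the intervention arm is a third option.

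For the secondary outcomes, the reference back attaches to the statistical methods. That it also carries attendance and fidelity is a possible reading, not stated text.

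**Conclusion.** Wrong as written. The sentence defines an analysis by allocation and then conditions it on two consequences of allocation. Under ordinary covariate adjustment with controls coded 0, the arm coefficient no longer estimates the effect of allocation.

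The result can be lost precision only (standard error from 0.13 to 0.20 with attendance, or 0.29 with both terms), a shift of about 0.2 SD in either direction, or removal of a 0.40 SD effect. Under no true effect with a prognosis link, type I error was roughly 16-23% with attendance alone and about 10% with both terms, where the larger standard error masks part of the same shift. These sizes are conditional illustrations that rest on assumed attendance, fidelity and prognosis links and on unclustered outcomes. The contradiction itself rests on none of them.

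**What to change.** In section f), delete level of attendance and programme fidelity from the primary-analysis sentence. Limit the primary model to allocation, the listed baseline characteristics and the clustering terms for group and for several children in one family. State that the secondary allocated-treatment analyses follow the same rule. Keep attendance in the supplementary efficacy analysis already planned, and examine fidelity only within the intervention arm.

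The cost is one sentence of wording, plus a short clause for the secondary outcomes. No data collection changes, and the sample size stays as it is. The change should be made before the outcome data are analysed by arm, so that the choice of model cannot depend on the results.

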### d) Intervention

The FLNP is a ten week programme involving 2 hour sessions each week for groups of 6-10 parents. The programme is structured and aims to provide experiential learning through the use of guided discussion, role play and home work. Parents set targets for themselves each week and report back on progress the following week. The course covers a wide range of behaviours and attitudes which parents may or may not choose to adopt. The ethos of the programme is that to empower parents to bring about changes in family life it is important to invite them to test different approaches and see which they can make work in their families, rather than providing prescriptive instructions.

The four building blocks of the programme are: the development of self-awareness and self-esteem, appropriate expectations, positive discipline, and empathy. The programme is eclectic, drawing on social learning theory and psychotherapeutic insights. It is founded on the belief that empathetic insight into emotional determinants of behaviour is important for both positive relationships and behaviour management. It aims to provide parents with insights into the origins of self-esteem and positive relationships by drawing on their own experiences as children. The programme thus supports parents in improving their own relationships with others as well as with their children. Parents are given a copy of the programme book 'The Parenting Puzzle' [37] and each programme is run by two trained facilitators who receive face to face supervision three times during the course of the programme from an experienced programme facilitator. The capacity to make compassionate relationships with the parents in the groups, to empower and to support them and at the same time provide a tightly run structured group programme is seen as essential to success [26,43].

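### The supplementary 'efficacy analysis' regresses outcomes on sessions attended, which families choose after randomisation, so its estimate is open to confounding in either direction

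*Protocol article*

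**What the plan says.** The main analysis in f) Analysis is by allocated treatment, "based on all families allocated to the intervention group regardless of whether they attended the programme". A supplementary analysis follows: the programme's capacity to bring about change in parents "will be assessed in a regression analysis based on numbers of sessions attended (efficacy analysis"). Secondary outcomes are handled in the same order, "adopting first an allocated treatment approach using mixed univariate and multivariate methods as above followed by an efficacy analysis".

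Three other statements bear on this:

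- Section d) Intervention sets the range of exposure: "The FLNP is a ten week programme involving 2 hour sessions each week", so 0 to 10 sessions.
- Section b) Sample size calculation fixes control exposure at zero up to the endpoint: "The control families are offered FLNP after data collection at six months 'post intervention' is complete". It also says that single families are the unit of randomisation and that non-attenders and dropouts are still followed up.
- Section e) Outcome measures lists "attendance rates (number of sessions attended") among the data collected. That is not an error; it means the data for a better analysis will exist.

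For the regression on sessions, the article names no use of the allocation, no covariates and no caution on interpretation.

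**The concern.** The stated aim and the label are causal, but the exposure is not randomised. The Discussion notes that parents are free to drop out of a group. Whatever makes a family stay, such as motivation, stability or severity of need, may also affect parenting scores and child wellbeing whether or not the programme works. A regression on sessions credits that difference to the programme.

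The Background says commissioners hesitate to fund the programme without randomised evidence. A weak allocated-treatment result printed beside a favourable 'efficacy' result on several outcomes could be read as evidence that the programme works for those who attend. If the families in most difficulty attend more, the same regression could make a useful programme look ineffective.

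**Working it through.** **1. The plan's own figure.** The article gives no number for the efficacy analysis, so only the sample size can be reproduced. For 0.4 SD, 85% power and two-sided alpha 0.05 (sidedness is assumed): n = 2(1.960 + 1.036)² / 0.4² = 17.95 / 0.16 = 112.2, so 113 per arm. With 20% loss, 113 / 0.8 = 141.25, so 142 per arm or 284 in total, against 288 stated. It reproduces. Analysed families: 144 × 0.8 = 115.2, so 115 per arm below.

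**2. Bias of a regression on sessions when the programme does nothing.** Let S be sessions attended, U the family's propensity to attend, and r the correlation of U with the outcome (in SD) the family would have had anyway.

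- Intervention arm only: slope = r·Cov(S,U) / Var(S).
- Both arms, controls at zero: slope = ½·r·Cov(S,U) / (½·Var(S) + ¼·mean(S)²).

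Assumed attendance (not in the article): 25% of intervention families attend nothing and the rest are spread evenly over 1 to 10 sessions, ranked by a normal propensity.

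- mean(S) = 0.75 × 5.5 = 4.125
- Var(S) = 0.75 × 38.5 − 4.125² = 28.875 − 17.016 = 11.859
- Cov(S,U) = 3.26 (the sum of the normal density at the ten cut points)

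False effect per 10 sessions:

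- Intervention arm only: 10 × 3.26 / 11.859 × r = 2.75 r
- Pooled: 10 × 1.63 / (5.930 + 4.254) × r = 1.60 r

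Simulation (4,000 runs, true effect zero, nominal 5% test) agrees:

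| r | Pooled, SD | Pooled, rejects | Intervention arm, SD | Intervention arm, rejects |
|---|---|---|---|---|
| 0 | 0.00 | 5.3% | 0.00 | 4.8% |
| 0.1 | 0.16 | 11.9% | 0.28 | 17.8% |
| 0.2 | 0.32 | 34.6% | 0.55 | 54.0% |
| 0.3 | 0.48 | 65.0% | 0.82 | 87.4% |
| 0.4 | 0.64 | 88.9% | 1.10 | 99.3% |
| −0.3 | −0.48 | 65.5% | −0.82 | 87.7% |

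The allocated-treatment comparison rejects in 4.5% to 6.0% of these runs. A pooled false effect equal to the planned 0.4 SD needs r = 0.4 / 1.60 = 0.25. At r = 0.3, with 10% or 40% never attending, the pooled regression rejects in 54% or 69% of runs.

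**3. A moderate scenario.** Suppose propensity to attend correlates 0.35 with a family trait, and the trait correlates 0.4 or 0.6 with the outcome. Then r = 0.35 × 0.4 = 0.14 or 0.35 × 0.6 = 0.21, and the pooled false effect is 1.60 × 0.14 = 0.22 SD or 1.60 × 0.21 = 0.34 SD. Simulation gives 0.23 and 0.34 SD, rejecting in 20% and 37% of runs. A pattern with a mean of about 5 sessions gives 0.19 and 0.27 SD. Hence about 0.2 to 0.3 SD.

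**4. Adjusting for the baseline outcome.** The share of bias left is roughly 1 − ρk. Here ρ is the baseline to follow-up correlation (0.7 assumed) and k is the baseline's association with attendance relative to that of the follow-up outcome.

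- k = 1: 1 − 0.7 = 0.30 remains. With a slightly stronger trait–attendance correlation (0.4), the pooled effect falls from 0.26 to 0.08 SD (rejection 24% to 8%) and from 0.38 to 0.12 SD (46% to 12%).
- k = 0.7: 1 − 0.49 = 0.51 remains. The step 3 figures become 0.51 × 0.23 = 0.12 and 0.51 × 0.34 = 0.17 SD, with rejection at 12% and 21% (roughly 16% to 34% using the intervention arm only).

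Hence about 0.1 to 0.2 SD after adjustment: smaller, but not reliably gone.

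**5. The allocation-based estimate.** With control attendance at zero, the instrumental estimate per 10 sessions is (allocated-treatment difference) × 10 / mean(S).

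- No true effect: it averages about 0.00 SD and rejects in 4.4% to 5.8% of runs for r from 0 to 0.4.
- True effect 0.4 SD per 10 sessions, r = 0.3: the allocated-treatment difference averages 0.162 SD, and 0.162 × 10 / 4.125 = 0.39 SD. The pooled regression averages 0.87 SD and the intervention-arm regression 1.22 SD.
- In that case the instrumental test rejects in 24.7% of runs and the allocated-treatment test in 22.3%: essentially the same test on another scale.

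**The case against.** The strongest reply is that the article fixes little. It does not say whether controls enter at zero, which covariates are used, or whether allocation serves as an instrument; two-stage least squares is itself a regression involving sessions. A condensed article may leave this to an analysis plan. That stands in part. A reader might infer that attenders are compared with everyone else, but the sample is not specified. The point survives because a regression on sessions carried out as written is confounded under either choice of sample.

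A reader might also infer that the article shows attendance to be driven by mistrust and disorganised lives. It does not. Its remarks on mistrust and poor attendance at meetings concern potential participants before enrolment, and its remarks on disrupted families concern loss to follow-up. Neither describes attendance at programme sessions. That attendance is prognostic is plausible, not documented.

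Three further objections stand. Baseline data are collected, and adjustment removes much of the bias in the scenarios above. The bias may run towards no effect. And an allocation-based estimate gives no independent test of benefit and no dose-response information, so a cautioned descriptive regression has a legitimate place beside it.

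**Conclusion.** The point holds as a flaw in a stated supplementary method: the estimate labelled 'efficacy' is open to confounding in either direction, for the primary and all other outcomes. Its size cannot be known from the article. The 0.2 to 0.3 SD unadjusted and 0.1 to 0.2 SD adjusted figures are for the pooled regression with no true effect. They rest on assumed attendance, assumed correlations and an assumed baseline correlation of 0.7; regression within the intervention arm alone gives larger figures.

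A reader might go further and infer that the trial's conclusion is at risk, or that the regression will necessarily favour the programme. The documents support neither. The allocated-treatment analysis comes first for every outcome and does not depend on this one, and the sign of the bias is not known.

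The main model is also described as "taking into account level of attendance, programme fidelity and differences in the characteristics of the two groups". Bringing attendance into the allocated-treatment model is a separate matter and adds no weight here.

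**What to change.** Define the efficacy estimate through random allocation: a complier average causal effect, or two-stage least squares with allocation as instrument for sessions attended or for a minimum attendance set in advance. Include baseline covariates and allow for FLNP group in the standard errors. State the exclusion restriction (allocation affects outcome only through attendance) and, if the number of sessions is used, linearity per session. Say that this estimate rescales the allocated-treatment effect and is not a second test of benefit.

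Keep any plain regression on sessions only as a descriptive, non-causal dose-response association, drop the word 'efficacy' for it, and say whether controls are included.

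The cost is a few lines of wording and no new data: attendance is recorded, non-attenders are followed up, and controls are not offered the programme until six-month data are complete. The downside is wider intervals and reliance on the stated assumptions.
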